#### Postintervention Period

All participants will have a 1-hour meeting with the researchers for the final data collection. We will collect the postintervention data with an MBG questionnaire [24], an engagement questionnaire [27], an acceptance questionnaire (TAM) [28], and a usability questionnaire (SUS) [29].

#### Statistical and Qualitative Analysis

Our expectation for the primary outcome is the reduction and stabilization of blood pressure. For the secondary outcome, we hope for acceptance of the eHealth platform and improvements in treatment adherence, physical activities, and dietary intake. A priori levels will be set according to the assessment tool and the expected outcome. The acceptance of the eHealth platform will consider good scores obtained in the analysis of usage logs and questionnaires of engagement, SUS, and TAM. Improved adherence to treatment will consider MBG questionnaire scores measured before and after the intervention. For the analysis of physical activities and dietary intake, a binary outcome will consider whether the patient has adequate levels, diagnosed according to the SISVAN’s questionnaire and standards.

For qualitative data, we will use Minayo’s guidelines [30]. Numeric data will be analyzed with statistical software SPSS 22 (IBM Corp, Armonk, New York). We will calculate the measures of central tendency and dispersion of the quantitative variables, and we will use the Kolmogorov-Smirnov test to verify normality. Basic quantitative data will be determined by mean, standard deviation, and median. Categorical data will be determined by simple frequency. Blood pressure data will be analyzed with the paired *t* test. Either the paired *t* test (parametric) or the Wilcoxon test (nonparametric) may be applied to compare other quantitative variables before and after the intervention. To assess treatment adherence, physical activity, and dietary intake after intervention, we will apply the Chi-square test while considering the app use as the dependent variable; the independent variables will be treatment adherence, physical activity, and dietary intake. For the MBG questionnaire, we will apply the Mann-Whitney test to compare the score between the groups before and after the intervention. The same test may be used to compare diastolic and systolic blood pressure measurements between the preintervention and postintervention groups. We will consider a 95% confidence interval (*P*<.05).

To evaluate the findings’ heterogeneity (primary and secondary outcomes), we will apply a statistical technique to verify whether the differences observed in the results can be explained by chance. We will apply the Chi-square test with a significance level of *P*<.10. The magnitude of heterogeneity will be assessed by calculating the I^2^ value, which ranges from 0% to 100%. An I^2^ greater than 50% indicates substantial heterogeneity, and an I^2^ above 75% indicates considerable heterogeneity. For the evaluation of heterogeneity, we will consider the demographic and socioeconomic variables. In the presence of heterogeneity, we will investigate its causes through sensitivity analysis. In the sensitivity analysis, the form of data analysis varies, to identify the impact of this change on the results. All analysis techniques can be adjusted or modified, if required, by the characteristics of the collected data. If feasible, we also intend to analyze the results with logistic regression of preintervention and postintervention data. In this case, the dependent variable will consider the base category *whether* [user] *used the app*, related to independent, categorized, and continuous variables of interest such as sociodemographic variables and the expected secondary outcomes.

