**Figure 2 figure2:**
[figure not shown]
Trial procedure flowchart. eHealth: electronic health; MBG: Martín-Bayarre-Grau; SUS: System Usability Scale; TAM: technology acceptance model.

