#### Evaluation and Assessment Frameworks

We will use the following assessment instruments:

Mini-Mental State Examination: It verifies the integrity of cognitive functions, assessing the functions of space-time orientation, memory, attention, calculus, language, and constructive praxis. It includes 11 tasks, with a score ranging from 0 to 30 points. Brucki et al [23] adapted it to the Brazilian context. The cut-off points relate to the years of schooling of the subjects, ie, for illiterate individuals, 19 points; 1-3 years of schooling, 23 points; 4-7 years of schooling, 24 points; and more than 7 years of schooling, 28 points.Sample characterization and sociodemographic questionnaire: It includes questions on age, level of education, income, and experience in using a blood pressure meter. The project researchers will provide the specifications.Martín-Bayarre-Grau questionnaire (MBG): It assesses the therapeutic adherence for arterial hypertension. Alfonso et al [24] developed and validated this instrument, and Matta et al [25] adapted it to the Brazilian Portuguese language.Dietary intake questionnaire by the Brazilian Food and Nutrition Surveillance System (SISVAN): from the Brazilian Ministry of Health [26], this questionnaire identifies the intake frequency of some foods and beverages over the last 7 days through 10 questions. Each item may relate to healthy food or nonrecommended unhealthy food.Engagement questionnaire: It assesses the attributes of engagement, such as esthetics, sensory appeal, concentration, awareness, challenge, control, feedback, interest, motivation, novelty, and time perception. O’Brien and Toms [27] proposed and validated the model, and Cechetti et al [17] translated it to Portuguese.Acceptance questionnaire: This is based on the technology acceptance model (TAM) [28]. The assessment relies on three categories: perceived utility (determines the degree to which a person believes the use of a technology may improve performance and productivity), ease of use (determines the degree to which a person believes the use of a system will be easy to learn and interact with), and external variables (provide understanding about what influences perceived utility and ease of use).Usability assessment questionnaire: This is in accordance with the System Usability Scale (SUS), related to the ease of use and use effort. Brooke [29] developed this framework.Comfort assessment questionnaire for the wearable device: It aims to verify the comfort and well-being of users while trying the wearable technology. The project researchers will produce this instrument.Characteristics of app use: It considers the number of accesses, number of records per period, response to notifications, and reminders. The system usage logs will calculate all this information. We will also use open questions so that participants can report their experience.Health professional assessment: We will perform a semistructured interview with health professionals to verify opinions on the characteristics and resources of the eHealth platform. Questions include, but are not limited to the following: (1) As a health professional, do you believe that the app and dashboard’s features can facilitate the clinical practice to monitor a patient? In what way? (2) Do you believe that a patient can benefit from the app’s features in his or her treatment? In what way? (3) What changes do you suggest for this platform to make it more useful or applicable to clinical practice?

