#### Preintervention Period

After verifying the inclusion criteria, all participants will have a 1-hour meeting with the researchers for instructions on the objective of the study and for signing a consent form detailing all the study procedures. We will register the participants of the intervention group in the system and instruct them about the app’s use. We will collect the preintervention data from both groups from a sample characterization questionnaire and an MBG questionnaire [24].

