#### Intervention Period

Participants from the control group will perform conventional hypertension monitoring using paper logbooks. Participants from the intervention group will use the app for 3 months, periodically registering the values of blood pressure, weight, height, sleep quality, waist circumference, mood, and heartbeats, among others. Health professionals from the health centers will assist the participants by using the website dashboard to monitor and interact with their patients. Professionals’ performance will not be evaluated, but we will ask them to participate by communicating with patients weekly on the platform. We will use all the data recorded by patients and health professionals during the intervention in the final analysis of results, especially the measurements of blood pressure and frequency of physical activity.

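### Diet and physical activity are classified by a questionnaire described as covering food only and missing from both visit lists, and the only firm test is an unadjusted postintervention Chi-square

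*Protocol article*

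**What the plan says.** All places are in the Methods of the protocol article.

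- **Outcome definition** (Statistical and Qualitative Analysis): "For the analysis of physical activities and dietary intake, a binary outcome will consider whether the patient has adequate levels, diagnosed according to the" SISVAN questionnaire and its standards. The same paragraph gives improvement in activity and diet as the hope for these secondary outcomes.
- **Instrument** (Evaluation and Assessment Frameworks): for SISVAN, "this questionnaire identifies the intake frequency of some foods and beverages over the last 7 days through 10 questions", and "Each item may relate to healthy food or nonrecommended unhealthy food".
- **First visit** (Preintervention Period): "We will collect the preintervention data from both groups from a sample characterization questionnaire and an MBG questionnaire". Of the characterization questionnaire the protocol says: "It includes questions on age, level of education, income, and experience in using a blood pressure meter".
- **Last visit** (Postintervention Period): "We will collect the postintervention data with an MBG questionnaire", followed by the engagement, TAM and SUS questionnaires.
- **Between visits** (Intervention Period): recorded data will be used, "especially the measurements of blood pressure and frequency of physical activity". The intervention group records in the app. The control group keeps paper logbooks for conventional hypertension monitoring.
- **Test** (Statistical and Qualitative Analysis): a Chi-square test for adherence, activity and diet after the intervention. A logistic regression of pre- and postintervention data is added only if feasible, with app use as the dependent variable.
- **Allocation** (Study Population and Sample): a patient with a compatible phone goes to the intervention group, and an otherwise eligible patient without one goes to the control group. A propensity score on age, gender and socioeconomic status is mentioned.

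**The concern.** Three parts of the plan do not fit together. The outcome definition relies on SISVAN for two constructs, but the protocol's description supports it for only one of them. The definition needs SISVAN data, but neither visit's list of named questionnaires provides for them. The aim is a change, but the firm test looks only at the end state.

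The last part matters more here than in a randomized trial. Phone ownership decides the group, and it may well go with age and income, which may in turn go with diet and activity. If the groups differ in adequacy at entry, the Chi-square test will report that difference as if it followed from the app. At stake are two secondary outcomes that the abstract names among the expected gains. Baseline answers not collected at the first meeting cannot be recovered later, whatever a later analysis plan says.

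**Working it through.** **1. Passages side by side**

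| Needed for the stated outcome | What the article provides |
|---|---|
| A diet instrument | SISVAN, listed among the instruments |
| An activity instrument and threshold | None named; SISVAN is described by food and beverage items only; the reference to its standards names no activity criterion |
| Diet and activity status at entry, both groups | Preintervention list: characterization questionnaire and MBG |
| Diet and activity status at 3 months, both groups | Postintervention list: MBG, engagement, TAM, SUS |
| Activity recorded alike in both groups | App record in the intervention group; contents of the control logbook not specified |
| A test of improvement | Chi-square after the intervention; pre/post logistic regression only if feasible |

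The conditional logistic regression does not fill the gap. Its dependent variable is app use, so it does not model adequacy as the outcome, and it needs baseline diet and activity data that no visit list includes. The paired *t* and Wilcoxon tests are assigned to quantitative variables, not to this binary outcome. The propensity score is not tied to the Chi-square test and contains no baseline diet or activity.

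**2. The plan's own figure**

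The article gives no sample size for diet or activity, so I take the number per group from the primary outcome: 80% against 40%, two-sided 5% (assumed two-sided), 80% power.

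- Uncorrected: n = [1.96 × √(2 × 0.6 × 0.4) + 0.842 × √(0.8 × 0.2 + 0.4 × 0.6)]² / 0.4² ≈ 22.3, so 23.
- With continuity correction: (22.3 / 4) × [1 + √(1 + 4 / (22.3 × 0.4))]² ≈ 27.1, so 28.
- Allowance: 28 × 1.2 = 33.6, so 34.

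The stated 28 and 34 are reproduced.

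**3. What a postintervention-only test does when the groups differ at entry**

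Assumptions, none of them in the documents: adequacy is 50% in one group and 45%, 40% or 35% in the other, and it stays unchanged in both, so the app has no effect.

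Normal approximation for 50% against 35%, 28 per group:

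- SE under equality = √(2 × 0.425 × 0.575 / 28) = 0.132
- SE under the assumed rates = √(0.5 × 0.5 / 28 + 0.35 × 0.65 / 28) = 0.131
- P(significant) ≈ P(Z > (1.96 × 0.132 − 0.15) / 0.131) = P(Z > 0.83) ≈ 0.20

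Exact enumeration of the two binomials, Pearson Chi-square at 5%:

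| Assumed baseline adequacy | 28 per group, uncorrected | 28 per group, continuity-corrected | 34 per group, uncorrected |
|---|---|---|---|
| 50% vs 50% | 4.5% | 2.3% | 4.5% |
| 50% vs 45% | 6.0% | 3.2% | 6.4% |
| 50% vs 40% | 10.9% | 6.3% | 12.6% |
| 50% vs 35% | 19.6% | 12.4% | 24.0% |

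A 5-point gap leaves the error rate near nominal. A 15-point gap raises it to about four times nominal without the correction, and more patients make it worse.

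**The case against.** The strongest reply is that this is a condensed article and silence is not exclusion. Much of that stands, and it rules out several stronger readings.

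- *A reader might infer that SISVAN will not be given at all.* The article says the listed instruments will be used, and SISVAN is among them. The visit lists also leave out blood pressure, the primary outcome, which will certainly be measured. What holds is that the visits at which SISVAN is given, and to whom, are not stated and must be reconciled with the outcome definition.
- *A reader might count the Figure 2 caption as further evidence,* since it expands MBG, SUS and TAM but not SISVAN. The figure is not shown, and a caption expands only the acronyms printed in it. I give it no weight.
- *A reader might state as fact that SISVAN has no activity items.* The questionnaire is not reproduced, and the outcome definition also refers to SISVAN's standards. What holds is that, as described, it covers food and drink, and that no activity instrument or threshold is named.
- *A reader might conclude that controls will have no activity data.* The fields of the paper logbook are unspecified, not excluded, and the sentence on using recorded activity is not limited to one group.
- *A reader might say that no pre/post analysis or confounder control is planned.* The conditional logistic regression and the propensity score show that both were considered. Neither is tied to the one firm test of these outcomes.
- *A reader might claim that the result will mostly reflect who owns a smartphone.* The documents give no baseline rates. The 20% figure rests on one assumed 15-point gap, and smaller gaps give far less.

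An analysis plan that is not shown could replace the test. It could not supply baseline data that were never collected.

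**Conclusion.** The point holds in this form. The outcome definition and the instrument description conflict on physical activity. The outcome definition and the visit lists are not reconciled on when SISVAN is given. The only firm test cannot separate an effect of the app from a difference at entry between groups formed by phone ownership.

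With no app effect, a spurious significant result would occur about 6%, 11% or 20% of the time for assumed baseline adequacy of 50% against 45%, 40% or 35% (28 per group, uncorrected; about 12% for the last with continuity correction). These figures show the range only; the actual baseline gap is unknown. The conflict between the passages does not depend on them.

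The outcomes are secondary, so the primary comparison is untouched. The change should still be made before enrolment, because it concerns data to be collected at the first meeting.

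**What to change.** 1. Reconcile the instrument list and the outcome definition with the two visit lists by stating that SISVAN (10 questions) is given to both groups at both existing 1-hour meetings.
2. Name an activity measure with its adequacy threshold, collected the same way in both groups at both meetings. Otherwise, withdraw activity as a between-group outcome and report the app record descriptively for the intervention group.
3. Replace the postintervention-only Chi-square for these outcomes with a comparison of 3-month adequacy by group, adjusted for baseline adequacy and the planned propensity score. Logistic regression with adequacy as the outcome and group as a covariate is one suitable form. With about 28 per group, entering the score as a single term keeps the model small.

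Cost: a few minutes per participant at each existing visit and a small amendment. No new visit is needed.

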#### Study Population and Sample

The study population will include men and women under treatment for arterial hypertension who will be assisted by health professionals in the public health system of a Brazilian city. After the invitation to take part in the study, the participants will sign a consent form. The effect (primary outcome) is expected to be 80% in the intervention group and 40% in the control group, which means a 40% difference. These proportions are based on the findings of the study by Neumann et al [22], which was conducted with a similar design, and also on more optimistic results obtained from one of our pilots [19]. For sample calculation, we used Epi Info version 6.0 software (Centers for Disease Control and Prevention, Atlanta, Georgia; sample size/2 proportions). We considered an estimate of 40% proportion difference between groups, 95% confidence interval, and 80% statistical power (beta). The calculation resulted in 28 individuals for each group, but to minimize the effects of loss and refusal during the intervention, we added 20% to the size, yielding a total of 34 individuals in each group.

The allocation of patients in each group will be based on the eligibility criteria. For example, if the patient fits all the criteria but does not have a mobile phone compatible with the app, then he or she will be allocated to the control group. If the patient has a mobile phone compatible with the app, he or she will be allocated to the intervention group. For propensity score calculation, based on the effect of confounding factors or predictors of exposure (to intervention), we will consider demographic variables of age, gender, and socioeconomic status.

We will consider the following inclusion criteria:

Cognitive ability confirmed by the Mini-Mental State Examination [23] (both groups)Current medical monitoring for the treatment of hypertension in the public health system of the city of Passo Fundo, RS, Brazil (both groups)Possibility to measure blood pressure in drugstores, hospitals, Family Health Strategies, or centers for comprehensive health care (both groups)Possession of an Android mobile phone, version 4.3 or higher (intervention group)Familiarity with the use of apps (intervention group)Internet access on the smartphone (intervention group).

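### Diet and physical activity are recorded as frequencies but cut to adequate yes/no for the only firm between-group test, which costs power

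*Protocol article*

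**What the plan says.** Acceptance of the platform, treatment adherence, physical activity and dietary intake are the secondary outcomes of the Protocol article (Statistical and Qualitative Analysis). For activity and diet, "a binary outcome will consider whether the patient has adequate levels", judged by the SISVAN questionnaire and standards. The test follows in the same section: "To assess treatment adherence, physical activity, and dietary intake after intervention, we will apply the Chi-square test", set against app use.

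The data are finer than that test. On the SISVAN dietary instrument, Evaluation and Assessment Frameworks says "this questionnaire identifies the intake frequency of some foods and beverages over the last 7 days through 10 questions". On the data going into the final analysis, Intervention Period says "especially the measurements of blood pressure and frequency of physical activity".

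Adherence is handled differently. It is measured by the MBG score before and after the intervention. Besides the Chi-square, the section prescribes a Mann-Whitney test of that score between the groups.

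Two other analyses could touch these outcomes. One is an optional paired t or Wilcoxon test of other quantitative variables before and after. The other is a logistic regression, planned only if feasible, with app use as the dependent variable.

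**The concern.** The stated hope is for improvement in diet and activity. A yes/no cut records only whether a patient is on the adequate side of the threshold after the intervention. A patient whose intake is better on several items but who stays below the threshold counts the same as one with no improvement. In a trial planned on 28 patients per group before losses, that discarded information can decide whether a real benefit on a secondary outcome is detected.

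For adherence the issue is duplication. One outcome is tested on two scales at P<.05, with no statement of which result counts if they disagree.

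**Working it through.** **1. The plan's own figure.** Study Population and Sample states: "The effect (primary outcome) is expected to be 80% in the intervention group and 40% in the control group". It then states: "The calculation resulted in 28 individuals for each group". Inputs: p1 = 0.80, p2 = 0.40, mean 0.60, two-sided 5% (sidedness is assumed), power 80%.

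- Uncorrected: n = [1.96·√(2·0.6·0.4) + 0.8416·√(0.8·0.2 + 0.4·0.6)]² / 0.4² = (1.358 + 0.532)² / 0.16 = 22.3, so 23.
- With continuity correction: n = (22.33/4)·[1 + √(1 + 4/(22.33·0.4))]² = 27.1, so **28**, as stated.
- Loss allowance: 28 × 1.2 = 33.6, so **34**, as stated.

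These figures size the primary outcome. The article gives no expected proportion, standard deviation or power for diet, activity or adherence.

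**2. Model for the cost of the cut (assumption).** The recorded measure is taken as normal with equal spread in both groups. It is cut so that a share p0 of controls and p1 of the intervention group are adequate. The implied shift is d = Φ⁻¹(p1) − Φ⁻¹(p0).

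**3. One case by formula: 70% vs 40%, n = 28 per group.**

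- d = 0.524 + 0.253 = 0.778.
- Full scale: Φ(d·√(n/2) − 1.96) = Φ(0.778·3.742 − 1.96) = Φ(0.95) = 83%.
- Cut: Φ{[0.3·√28 − 1.96·√(2·0.55·0.45)] / √(0.21 + 0.24)} = Φ[(1.587 − 1.379)/0.671] = Φ(0.31) = 62%.
- Loss: about 21 points.

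**4. Simulation (20,000 runs, n = 28 per group, two-sided 5%, Chi-square without continuity correction).** Losses were computed before rounding, so they can differ by 0.1 from the columns.

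| Adequate, intervention vs control | d | Mann-Whitney | t test | Chi-square | Loss vs Mann-Whitney | Loss vs t |
|---|---|---|---|---|---|---|
| 50% vs 40% | 0.25 | 14.9% | 15.8% | 11.2% | 3.8 | 4.7 |
| 60% vs 40% | 0.51 | 43.6% | 46.1% | 31.0% | 12.6 | 15.1 |
| 70% vs 40% | 0.78 | 79.2% | 81.8% | 61.1% | 18.1 | 20.6 |
| 80% vs 40% | 1.09 | 97.4% | 98.1% | 88.0% | 9.4 | 10.1 |
| 60% vs 30% | 0.78 | 79.2% | 81.6% | 60.7% | 18.5 | 21.0 |
| 40% vs 20% | 0.59 | 55.5% | 58.4% | 38.2% | 17.2 | 20.2 |
| 80% vs 60% | 0.59 | 55.4% | 58.1% | 37.9% | 17.6 | 20.2 |
| 90% vs 70% | 0.76 | 76.9% | 79.7% | 46.9% | 30.0 | 32.8 |

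For cuts at 20% to 60% of controls the loss runs from 3.8 points (Mann-Whitney, 50% vs 40%) to 21.0 points (t test, 60% vs 30%). The off-centre cut costs 30 to 33.

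**5. Sensitivity.**

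- With all 34 per group analysed, the loss against Mann-Whitney is 5.1 points at 80% vs 40% (99.1% vs 94.0%), 15.6 at 70% vs 40%, and 28.7 at 90% vs 70%.
- A continuity-corrected Chi-square at 28 per group widens the loss to 17.0, 29.2 and 21.5 points for 80%, 70% and 60% vs 40%.
- Coarsening the score to 8 ordered values, as in 0 to 7 days, moved Mann-Whitney power by at most about 1 point in a separate run of 5,000 (97.4% to 97.2%, 79.1% to 77.9%, 42.8% to 42.7%).

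**6. What the named analyses secure.** The paired t or Wilcoxon option compares before with after, not group with group. The regression is conditional on feasibility. For diet and activity, only the Chi-square on the cut outcome is a firm between-group test. For adherence, the Mann-Whitney on the uncut MBG score is also firm.

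**The case against.** The strongest defence is that the cut comes from an external standard and was not chosen from the data. A percentage adequate is easy to read, and no total SISVAN score is described, so a composite would have to be constructed. That stands as a reason to keep reporting the percentage and to define any summary score before analysis. It does not require the group test itself to be binary, and the items can also be compared one by one.

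A second objection concerns activity. The frequency named under Intervention Period is recorded during the intervention, the adequacy judgement comes from SISVAN, and controls use paper logbooks. The article does not show that both groups record activity in the same way, and setting app logs against paper could introduce a measurement difference. This stands and limits the fix.

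A third is that the regression admits continuous variables and the secondary outcomes. So it would be wrong to infer that no full-scale analysis is mentioned at all. Being conditional, however, it does not secure one.

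A reader might also infer that adherence loses power in the same way. It does not, because the Mann-Whitney test on the MBG score is already planned.

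**Conclusion.** The point holds for dietary intake and physical activity. Both are collected as frequencies, and the only firm between-group test uses a yes/no cut. At 28 per group, with a normal underlying score, the cost is about 4 to 21 points of power for cuts at 20% to 60% of controls, and about 30 for an off-centre cut such as 90% vs 70%.

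These are illustrations under assumptions, not figures from the article. A reader might take one narrow band, such as the 9 to 18 points seen at 60% to 80% vs 40% against Mann-Whitney, as the loss itself. The article does not support that, because it gives no effect size or cut position for these outcomes. The full scale does not rescue every case either: at 60% vs 40%, Mann-Whitney reaches only about 44%.

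For adherence the defect is a duplicate, weaker test and nothing more. Nor do the documents support reading this as a flaw in the trial's size, since 28 and 34 per group reproduce and concern the primary outcome.

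**What to change.** In Statistical and Qualitative Analysis:

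- **Diet:** make the main between-group test a comparison of the recorded SISVAN frequencies, item by item or through a summary score defined before analysis. Use Mann-Whitney, or an ordinal or linear model where adjustment for the preintervention value is wanted. Adjust only where that value is collected; the questionnaires listed under Preintervention Period are sample characterization and MBG.
- **Physical activity:** do the same only where its frequency is recorded by the same method in both groups.
- **Percentage adequate:** keep it, by the SISVAN standard, as a descriptive result per group.
- **Adherence:** delete it from the Chi-square sentence, so that the MBG score comparison is its only test.

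The cost is wording, plus defining any diet score in advance. No further patients are needed. A score difference is less direct to read than a percentage, which is why the percentage stays in the report.

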**Methods:**

The platform will include a server that centralizes all the data and business rules, a website dashboard for health professionals, and a mobile app for patients. We will analyze the effects of its use through a controlled, nonrandomized, nonblind, prospective, monocentric clinical trial. We will enroll 68 participants diagnosed with arterial hypertension and under medical follow-up and categorize them into two groups. The participants of the intervention group will use the platform as a monitoring method, whereas the participants of the control group will use conventional methods. In both groups, we will assess and compare the evolution of blood pressure and treatment adherence before, during, and after the intervention.

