### Nonrandomized Controlled Trial

This is an applied research of technological innovation with software development and analysis of its effects through a controlled, nonrandomized, nonblind, prospective, and monocentric clinical trial. The Research Ethics Committee of the University of Passo Fundo, Rio Grande do Sul, Brazil (report 3.414.793) approved this project, which was registered in the Brazilian Platform of Clinical Trials under the code RBR-2rkkgn (Universal Trial Number U1111-1230-7550). Figure 2 presents the trial design and flowchart.

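### No between-group test of blood pressure is firmly committed to as the primary analysis; the only definite test is a within-participant paired t test

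*Protocol article*

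**What the plan says.** All places are in the Protocol article.

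- **Primary outcome** (Statistical and Qualitative Analysis): "Our expectation for the primary outcome is the reduction and stabilization of blood pressure".
- **Definite test** (same section): "Blood pressure data will be analyzed with the paired" *t* test.
- **Optional test** (same section): the Mann-Whitney test is first assigned firmly to the adherence questionnaire, where "we will apply the Mann-Whitney test to compare the score between the groups before and after the intervention". Blood pressure then follows in permissive terms: "The same test may be used to compare diastolic and systolic blood pressure measurements between the preintervention and postintervention groups".
- **Design** (Nonrandomized Controlled Trial): a "controlled, nonrandomized, nonblind, prospective, and monocentric clinical trial".
- **Stated intent** (Abstract, Methods): "In both groups, we will assess and compare the evolution of blood pressure and treatment adherence before, during, and after the intervention".
- **Sample size** (Study Population and Sample): "The effect (primary outcome) is expected to be 80% in the intervention group and 40% in the control group, which means a 40% difference". This gives 28 per group, raised by 20% to 34.
- **Confounding** (same section): patients are allocated by whether they own a compatible phone. A propensity score on age, gender and socioeconomic status is planned, but no blood pressure analysis is said to use it.
- **Regression** (end of the analysis text): a logistic regression is intended if feasible. App use is the dependent variable, and blood pressure is not named among the example covariates.

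**The concern.** A paired test asks whether mean blood pressure changed over 3 months in the participants tested. The trial asks whether it changed more with the platform than with paper logbooks. Regression to the mean, usual care, more frequent measurement and study attention can lower pressure in both arms, and a paired test cannot separate these from a platform effect. Running it once in each arm does not help: a significant result in one arm and a nonsignificant result in the other is not a test of the difference between them.

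At stake is the primary conclusion. The patient numbers are justified by one contrast, between groups, while the only committed test addresses another, within participants. The same analysis text also lets any technique be changed in the light of the data, so no between-group blood pressure test is fixed in advance.

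**Working it through.** **1. The sample size is a between-group calculation.** Inputs from Study Population and Sample: p1 = 0.80, p2 = 0.40, 95% confidence (taken as two-sided alpha 0.05), power 80%.

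Uncorrected: n0 = [1.960·√(2·0.6·0.4) + 0.842·√(0.8·0.2 + 0.4·0.6)]² / 0.4² = (1.358 + 0.532)² / 0.16 = 22.3, so 23.

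Continuity-corrected: n = (n0/4)·[1 + √(1 + 4/(n0·0.4))]² = (22.3/4)·(1 + 1.203)² = 27.1, so **28 per group**, as stated. Then 28 × 1.2 = 33.6, so **34**, as stated. The figure reproduces exactly as a comparison of two independent proportions; it is not a calculation for a paired *t* test.

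**2. The paired test when the platform adds nothing.** The document gives no expected change or SD for blood pressure, so the fall is an assumption. Let both arms fall by the same d, in units of the SD of individual change. The paired *t* statistic in one arm is noncentral *t* with n − 1 degrees of freedom and noncentrality d·√n. A significant fall has probability P = Pr(T > t0.975, n−1), with critical value 2.052 at n = 28 and 2.035 at n = 34. If each arm is tested separately, the chance of a significant fall in the intervention arm and not in the control arm is P(1 − P).

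| Common fall d | P, n = 28 | P(1−P), n = 28 | P, n = 34 | P(1−P), n = 34 |
|---|---|---|---|---|
| 0.2 SD | 17.4% | 14.4% | 20.4% | 16.2% |
| 0.3 SD | 33.4% | 22.2% | 39.7% | 23.9% |
| 0.4 SD | 53.2% | 24.9% | 62.0% | 23.6% |
| 0.5 SD | 72.3% | 20.0% | 80.8% | 15.5% |

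In mmHg, an assumed common fall of 5 with an SD of change of 12, 15 or 18 (d = 0.42, 0.33, 0.28) gives 57%, 40% or 29% at n = 28.

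**3. The between-group test in the same situation.** In a two-sample *t* test on change scores the common fall cancels. Simulation (20,000 runs; falls of 0, 0.3 and 0.5 SD; n = 28 and 34) gave rejection rates of 4.9% to 5.4%.

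**4. What a between-group test on a continuous measure can detect.** Solving the noncentral *t* for 80% power, with 2n − 2 degrees of freedom and noncentrality d·√(n/2), gives d = 0.76 SD of change at n = 28 and 0.69 SD at n = 34. For an assumed SD of 12, 15 or 18 mmHg this is 9.1, 11.4 or 13.7 mmHg at n = 28, and 8.3, 10.3 or 12.4 mmHg at n = 34, before any gain from baseline adjustment.

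**The case against.** The strongest reply is that the authors clearly mean to compare the groups. The abstract says so. The paired test is not restricted to the intervention arm. A propensity score has a purpose only in a between-group comparison. The blood pressure Mann-Whitney sentence directly follows a between-group use of that test, and since paired data already have the paired *t* or Wilcoxon test, it is plausibly a loose wording of the same between-arm comparison.

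Most of this stands. A reader might infer that the control group is never used; the document does not support that. A reader might also infer that the authors will count a significant within-group fall, or significance in one arm only, as proof of benefit. No such rule is written, so the percentages above show what could happen if the committed test were read that way.

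It does not close the gap. An intent in the abstract names no test. The Mann-Whitney sentence is permissive and names timepoints, not arms; read literally, it applies an independent-samples test to before-after data. The propensity score is attached to no blood pressure analysis, and the logistic regression is conditional and does not name blood pressure.

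It is also fair to object that making continuous systolic pressure primary would choose a new endpoint and cut the link to the two-proportion sample size. The fix allows for that.

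**Conclusion.** The concern holds in this form: the plan firmly commits to no between-group test of its primary outcome. The one definite test is within participants, which does not match the controlled design, the stated comparison or the basis for 28 per group. This is a conflict within the document, not a detail left to an unseen analysis plan.

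The illustrated size is a 17% to 72% chance of a significant fall in the intervention arm without any platform effect, against about 5% between groups. It rests on 28 evaluable patients per arm, normally distributed changes, and an assumed equal fall of 0.2 to 0.5 SD; the document supplies neither fall nor SD, and the result depends strongly on their ratio. The 5% also assumes that both arms share the same expected change. Allocation by phone ownership does not guarantee this, so an unadjusted between-group test would not be enough.

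**What to change.** Replace the paired *t* test as the primary analysis with one committed between-group comparison by allocated group, adjusted for baseline blood pressure and the planned propensity score, and report the difference with its 95% CI. The outcome can be settled in either of two ways:

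- **Responder outcome.** Define the response behind 80% versus 40% and compare adjusted proportions between groups. This keeps the link to the 28 per group.
- **Continuous outcome.** Name one blood pressure measure as primary, fit a linear model on group, baseline and propensity score, and replace the sample size justification with the difference that 28 to 34 per group can detect (about 0.76 to 0.69 SD of change at 80% power before baseline adjustment).

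In either case make the other blood pressure measure secondary, keep paired tests as description only, and reword or remove the optional Mann-Whitney sentence for blood pressure.

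The cost is a change of wording plus one decision on the outcome, provided that comparable baseline and end-of-intervention readings exist in both arms. The downsides should be stated openly. Some confounding from allocation by phone ownership will remain after adjustment for age, gender and socioeconomic status, and under the continuous option the detectable difference is large.
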